# Short-term inhalation of xenon during anesthesia for prevention of postoperative delirium in elderly patients undergoing laparoscopic radical colectomy: study protocol for a randomized controlled clinical trial

**DOI:** 10.1186/s13063-024-08290-8

**Published:** 2024-07-02

**Keywords:** Xenon, Postoperative delirium, Laparoscopic radical colectomy, Elderly patients

## Abstract

**Background:**

Postoperative delirium (POD) is a common complication that is characterized by acute onset of impaired cognitive function and is associated with an increased mortality, a prolonged duration of hospital stay, and additional healthcare expenditures. The incidence of POD in elderly patients undergoing laparoscopic radical colectomy ranges from 8 to 54%. Xenon has been shown to provide neuroprotection in various neural injury models, but the clinical researches assessing the preventive effect of xenon inhalation on the occurrence of POD obtained controversial findings. This study aims to investigate the effects of a short xenon inhalation on the occurrence of POD in elderly patients undergoing laparoscopic radical colectomy.

**Methods/design:**

This is a prospective, randomized, controlled trial and 132 patients aged 65–80 years and scheduled for laparoscopic radical colectomy will be enrolled. The participants will be randomly assigned to either the control group or the xenon group (*n* = 66 in each group). The primary outcome will be the incidence of POD in the first 5 days after surgery. Secondary outcomes will include the subtype, severity, and duration of POD, postoperative pain score, Pittsburgh Sleep Quality Index (PQSI), perioperative non-delirium complications, and economic parameters. Additionally, the study will investigate the activation of microglial cells, expression of inflammatory factors in colon tissues, plasma inflammatory factors, and neurochemical markers.

**Discussion:**

Elderly patients undergoing laparoscopic radical colectomy are at a high risk of POD, with delayed postoperative recovery and increased healthcare costs. The primary objective of this study is to determine the preventive effect of a short xenon inhalation on the occurrence of POD in these patients.

**Trial registration:**

Chinese Clinical Trial Registry ChiCTR2300076666. Registered on October 16, 2023, http://www.chictr.org.cn.

**Supplementary Information:**

The online version contains supplementary material available at 10.1186/s13063-024-08290-8.

## Background

Colorectal cancer is the third most common cancer worldwide and is more prevalent among old population. More than 1.9 million new colorectal cancer cases and 935,000 deaths are estimated to occur in 2020, representing about one in 10 cancer cases and deaths [1]. Radical resection remains the primary treatment for colon cancer, and laparoscopic surgery has been shown to enhance recovery after surgery, reduce the occurrence of complications, and shorten the duration of hospital stay compared to open surgery [2, 3]. Both advances in minimally invasive surgical techniques and improvements in anesthetic care have provided more opportunities to undergo surgical treatment for elderly frail patients. However, available evidence indicates that elderly patients undergoing laparoscopic radical colectomy are at high risk of Postoperative delirium (POD), which is the main reason for delayed postoperative recovery and is associated with increased mortality and healthcare resource expenditure [4–8].

POD is a common and serious postoperative complication characterized by acute and fluctuating impairment in awareness and attention. Elderly patients with colon cancer are considered to be at a higher risk of POD due to the existence of various predisposing risk factors, such as preoperative cognitive impairment, malnutrition, comorbidities, polypharmacy, impaired functional status, and frailty, which accumulate and overlap with aging [7, 8]. In addition to the factors mentioned above, colectomy may trigger a cascade of events, including intestinal ischemia–reperfusion injury, disruption of the intestinal barrier, and inflammatory responses mediated through the inflammatory signaling in the gut-brain axis. This phenomenon is often referred to as the “two-hit model” of the surgical procedure [9]. These factors collectively exacerbate the onset of POD, especially in elderly patients who are more vulnerable [10]. Therefore, it is crucial to explore effective interventions of POD in these patients.

Updated guidelines issued by the European Society of Anesthesiology and American Geriatrics Society mainly focus on non-pharmacological interventions, such as preoperative physical conditioning and psychological interventions [11, 12], which may not be applicable for patients with colon cancer requiring surgical treatments as soon as possible. Thus, it seems more feasible to address the perioperative precipitating factors for these patients, especially in terms of clinically feasible pharmacological interventions.

Xenon, a noble gas with stable chemical properties and an excellent safety profile, has been used in clinical practice for over 70 years [13, 14]. It has been demonstrated that xenon can provide neuroprotection in vitro and in vivo neural injury models [15]. The neuroprotection of xenon is mainly attributable to antagonism at the N-methyl-D-aspartate (NMDA) subtype of the glutamate receptor [15]. Moreover, stable hemodynamic and rapid clearance properties of xenon make it less neurotoxic compared to conventionally used inhalational anesthetics [16–18]. In addition, xenon possesses an anti-inflammatory effect that may interfere with the pathogenesis of POD [19–21]. Considering that the neuroprotective mechanisms of xenon primarily target the pathophysiology of POD in elderly patients undergoing laparoscopic radical colectomy, we hypothesize that short-term xenon inhalation during anesthesia can reduce the occurrence of POD in these patients.

In addition to the incidence of POD, the outcome measures will also include several secondary endpoints, such as the subtype, severity, and duration of POD, postoperative pain score, Pittsburgh Sleep Quality Index(PSQI), perioperative non-delirium complications, and economic parameters. Furthermore, this study will measure the activation of microglial cells, expression of inflammatory factors in colon tissues, and levels of plasma inflammatory factors and neurochemical markers in order to explore the potential mechanisms of xenon to decrease the occurrence of POD.

## Methods/design

### Objectives and design

This prospective, randomized, controlled trial aims to test the hypothesis that short-term inhalation of xenon during anesthesia will reduce the incidence of POD in elderly patients undergoing elective laparoscopic radical colectomy. The study will enroll patients aged 65 to 80 years and scheduled for laparoscopic radical colectomy at Beijing Friendship Hospital, Capital Medical University, China. Participants will be randomly assigned to either the xenon group or the control group. The trial will adhere to the ethical principles and the trial protocol has been approved by the Ethics Committee of Beijing Friendship Hospital, Capital Medical University, China (Approval No: 2023-P2-100–03). The trial protocol has also been registered at the Chinese Clinical Trial Registry (Registration No: ChiCTR2300076666). Figure 1 shows the flow diagram of the study. The observatory will conduct screening based on established criteria and a pre-standard treatment plan. Data collection will commence with the accumulation of basic data and continue until the end of the follow-up (Table 1). We followed the SPIRIT reporting guidelines, and the (SPIRIT) 2013 Checklist is provided in Additional file 1.

**Fig. 1 Fig1:**
[figure not shown]
Flow diagram of the study

**Table 1 Tab1:**
[figure not shown]
Standard Protocol Items: Recommendations for Interventional Trials (SPIRIT) schedule for enrollment, interventions, and assessments

*PD* Postoperative day

### Sample size calculations

The primary endpoint is the incidence of POD in the first 5 postoperative days. Based on the unpublished retrospective observational study enrolled 49 patients in Beijing Friendship Hospital, Capital Medical University, China, the incidence of POD in elderly patients undergoing elective laparoscopic radical colectomy was 35.7%, while it was 14.3% in the other elective laparoscopic surgery. We hypothesize that short-term inhalation of xenon during anesthesia can reduce the incidence of POD down to the same level as patients in the other elective laparoscopic surgery. To achieve a power of 80% with a two-tailed alpha of 0.05, 61 patients are at least needed in each group. Considering 8% potential dropouts or losses to follow-up, we will enroll 66 patients in each group, leading to a total sample size of 132 patients.

### Inclusion criteria

Patients aged 65 to 80 years.Patients undergoing elective laparoscopic radical colectomy.American Society of Anesthesiologists (ASA) physical status classifications I to III.Able to read and understand the research materials.

### Exclusion criteria

History of severe allergies to xenon or other anesthetics.History of psychiatric disorders, such as depression, anxiety disorder, schizophrenia, and mood disorders.Presence of cognitive impairment at baseline as screened with the Mini-Mental State Examination (MMSE) (< 24 for education less than postsecondary education, < 23 for below secondary education; < 20 for less than primary education, or < 18 for illiteracy) [22].History of alcohol or drug abuse.Contraindications to laparoscopic surgery.Severe heart, liver, kidney, or respiratory dysfunctions.Urgent or emergent surgery.Unable to cooperate or difficulties in communication.Planned postponed tracheal extubation or transferred to ICU after surgery.The operation time > 6 h.Enrolled in other clinical trials simultaneously.

### Recruitment

According to inclusion/exclusion criteria, patients undergoing elective laparoscopic radical colectomy in Beijing Friendship Hospital, Capital Medical University, China, will be screened by the anesthesiologist the day before surgery. The anesthesiologist will explain the process, risks and benefits of this trial, and the collection of participant data to the candidate patients who achieve the eligibility criteria. After consent is obtained, the patients will be recruited for this trial and sign the written informed consent by themselves or their authorized clients. The subject may withdraw from the study at any time and for any reason. Moreover, the trial should be terminated, if serious adverse events (AEs) occur. The reasons and circumstances for dropouts will be recorded in the Case Report Form (CRF).

Given that our hospital performs 400 to 500 elective laparoscopic radical colectomies per year, the trial period is set at 12 months to ensure the recruitment of a sufficient number of participants. The first participant was enrolled on November 20, 2023, and the enrollment period is expected to be completed by December 2024. When half of the cases have been collected, we will estimate the recruitment rate and adjust the trial period accordingly.

### Blinding and randomization

The eligible patients will be randomized to either the control group or the xenon group using a computer-generated randomization sequence. Randomization will be performed in a 1:1 ratio, and allocation will be concealed using sealed envelopes. Both the study subjects and investigators assessing outcomes will be blinded to group assignments, and the study statisticians will perform the data analysis after the trial is completed.

### Standard procedure

#### Preoperative evaluation

All patients will be visited and examined the day before surgery. Demographic data including education levels, medical history, current medications, and results of physical and laboratory examinations will be collected and analyzed. Signs and symptoms of preoperative cognitive impairments will be assessed preoperatively with MMSE [22]. Frailty of the patients at baseline will be measured by means of a multidimensional frailty score [23]. Preoperative sleep disturbances at base will be calculated with PSQI [24].

#### Interventions

After the sealed randomization envelopes are opened, patients will be randomly allocated to the two groups:Patients in the control group will receive conventional anesthesia management.Other than the conventional anesthesia management, patients in the xenon group will also receive 50% xenon inhalation in the first 15 after anesthesia induction, using a closed-circuit xenon delivery system integrated with the anesthesia machine, according to the methods described in our previous work [25].

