### Statistical analysis

Statistical analysis will be conducted using SPSS 23.0 software by qualified statisticians from the clinical research center of Beijing Friendship Hospital. Due to the need for repeated evaluations of patients during the trial process, which may affect patient compliance, we will analyze the outcomes using both the Full Analysis Set (FAS) and the Per-Protocol Set (PPS) and compare the results from both analyses. The FAS will include all participants who are randomized according to the intention-to-treat principle, regardless of whether they strictly adhered to the trial protocol. Missing values in the FAS will be processed using the Last Observation Carried Forward (LOCF) method. The PPS will be defined as the population who strictly followed the trial protocol. This dual approach ensures a comprehensive assessment of xenon’s effectiveness, considering both generalizability and protocol adherence.

All statistical tests will be 2-sided, and a *p* value < 0.05 will be considered to indicate statistical significance. The choice of statistical tests will depend on the types and distributions of the parametric data.

The primary outcome, incidence of POD within the first postoperative 5 days, will be analyzed using *χ*^*2*^ tests.Categorical secondary outcomes, including subtypes of POD; the rates of intraoperative hypotension, hypertension, tachycardia, bradycardia, and arrhythmia; postoperative sleep disorder; and non-delirium complications, will also be analyzed with the* χ*^*2*^ test.Parametric data will also be tested for homogeneity of variance by using the Levene median test. If the data follow a normal distribution and exhibit homogeneity of variance, they will be expressed as mean ± standard deviation and compared between groups using the *t*-test. When data do not meet the criteria for normal distribution or have uneven variances, they will be presented as median (interquartile range) and compared between groups using the Mann–Whitney *U* test.The within-group comparisons of data at multiple time points will be performed with the repeated-measures ANOVA.Time-to-event outcomes, such as the duration of POD and hospital stay, will be analyzed using the log-rank test.The logistic regression analysis will be utilized to examine the factors influencing the primary outcome between groups while controlling for covariates, such as preoperative frailty score, postoperative pain, and pre- and postoperative sleep disturbances.

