To mitigate these disparities, several improvements have been in the protocol. Firstly, the heterogeneity among study subjects is a critical factor contributing to inconsistent research conclusions. For instance, while a randomized clinical trial in patients undergoing elective off-pump coronary artery bypass graft surgery demonstrated a significant reduction in POD incidence with 50–60% xenon anesthesia [34], similar benefits were not observed in studies involving on-pump cardiac surgery [35] or hip fracture surgery [36]. Variations in patient age, surgical types, and comorbidities contribute to these discrepancies. In order to avoid these confounding factors, we focus on elderly patients undergoing laparoscopic radical colectomy, a high-risk and extremely vulnerable patient group for POD [6–9]. And patients with surgery durations exceeding 6 h and those planned for postoperative ICU admission are excluded to minimize variability in surgical procedures and reduce selection bias. Secondly, practical considerations during trial implementation have been carefully taken into account. For example, administering multiple questionnaires over five consecutive days postoperatively may lead to patient fatigue and non-compliance. Therefore, outcomes will be analyzed using both FAS and PPS, providing comprehensive and robust results to better understand xenon's potential protective effects. This approach enhances the reliability of the trial and aids in identifying and addressing potential biases and data variability. And the logistic regression analysis will be utilized to examine the high-risk factors influencing the primary outcome between groups, such as preoperative frailty score, postoperative pain, and pre- and postoperative sleep disturbances. Moreover, considering the high cost of xenon is a significant barrier to its clinical research and widespread adoption, xenon will be administered only for a short time, that is, 1 h after anesthesia induction, a period associated with a higher likelihood of hemodynamic instability [37–39].

Despite the inability to blind the anesthesiologist due to the use of a closed-circuit xenon delivery system integrated with the anesthesia machine, strict adherence to a standardized hemodynamic treatment protocol will ensure equivalent management in both groups and minimize bias. Additionally, both investigators and study statisticians assessing primary and secondary outcomes will be blinded to group assignments.

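### The Interventions section and the Discussion give incompatible durations for the xenon exposure, so the exposure under test and adherence to it cannot be read from this protocol

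*Protocol article*

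**What the plan says.** The hypothesis, under Objectives and design, is that "short-term inhalation of xenon during anesthesia will reduce the incidence of POD". It gives no number for the length of exposure. The abstract, the Background and the closing part of the Discussion likewise call the exposure only short or short-term.

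Two places give a figure:

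- Interventions, the operational section: xenon patients "will also receive 50% xenon inhalation in the first 15 after anesthesia induction". For the delivery method, the same sentence points to the group's own earlier publication.
- Discussion, where the cost of xenon is given as the reason for limiting its use: "xenon will be administered only for a short time, that is, 1 h after anesthesia induction".

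Under Statistical analysis, outcomes are to be analysed in two sets and the results compared. For the first, "The FAS will include all participants who are randomized according to the intention-to-treat principle", whatever the adherence. For the second, "The PPS will be defined as the population who strictly followed the trial protocol". The article adds no exposure criterion to the latter definition.

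Trial status reports 30 participants recruited and describes this as the third protocol version, whose revisions concerned the secondary outcomes. Data management plans an unblinded interim analysis when nearly half of the cases in each group are complete.

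**The concern.** Duration is a main component of the exposure being tested, and a trial of a brief exposure depends on how brief it is. With two durations in current text, a reader cannot say which one a positive or a null result would support.

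The second consequence is for the per-protocol set. Its only stated rule is strict adherence to the protocol, so any judgement about length of exposure needs a single duration to judge against. This analysis is to be reported beside the full analysis set, so a planned result depends on it.

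Timing adds some weight. If the duration criterion were settled only after the interim unblinding, it would be chosen by people who could know the results by group.

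**Working it through.** **1. Do the two statements agree under any unit?** The inputs are 15 (Interventions, unit absent) and 1 h (Discussion).

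| Unit assumed for 15 | Comparison with 1 h = 60 min = 3,600 s | Agrees? |
|---|---|---|
| minutes | 60 / 15 = 4, so the Discussion figure is four times as long | no |
| seconds | 3,600 / 15 = 240, so 240 times as long | no |
| hours | 15 h is 15 times as long as 1 h, and cannot fit an operation when the exclusion criteria list "The operation time > 6 h" | no |

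Minutes is the natural reading, but it remains an assumption. The conflict does not depend on it; only the factor of four does.

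**2. Could 1 h be a time point and not a duration?** The Discussion sentence equates the hour with the short time for which xenon is given, and goes on to describe it as a stretch in which unstable haemodynamics are more likely. It reads as a duration.

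**3. Is one figure superseded?** Trial status attributes the revisions to secondary outcomes and reports no change to the intervention. Both figures stand in current text.

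**4. What follows for the per-protocol set?** Taking minutes as the unit:

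| Exposure delivered | Against Interventions | Against Discussion |
|---|---|---|
| 15 min | complies | deviates |
| 60 min | deviates | complies |

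The same patient is in or out according to the section consulted. Adherence criteria unrelated to duration are not touched by this.

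**5. Does the sample size depend on duration?** The Sample size section gives rates of 35.7% and 14.3%, two-sided alpha 0.05, power 80% and equal groups. With unpooled variances:

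n = (1.960 + 0.842)² × (0.357 × 0.643 + 0.143 × 0.857) / (0.357 − 0.143)² = 60.3, so 61 per group.

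This is the plan's figure. Adding 8% gives 61 × 1.08 = 65.9, so 66, also as stated. (Dividing by 0.92 gives 66.3, so 67, which is not the issue here.) Duration enters neither step.

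**6. Is there still time before the interim?** Half of 66 is 33 per group. With 30 recruited in both groups together, that point had not been reached when the article was written.

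**The case against.** The strongest reply is that this is a slip in a condensed article. The text was read from a PDF by a program, so the missing unit may be an extraction loss and cannot be held against the plan. The Interventions section does fix the gas, its concentration, the start after induction, the delivery system and the comparator. The trial runs at one centre under an approved protocol that is not shown, and staff there may have used one duration throughout. Detailed per-protocol criteria commonly belong in an analysis plan.

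Much of this stands. Four stronger readings are tempting, and the documents support none of them:

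- That the experimental treatment as a whole is undefined. Only its duration is inconsistent.
- That the per-protocol set is undefined. It is defined in general terms; what cannot be decided is its duration criterion.
- That the xenon arm already contains mixed exposures, or that all 66 xenon patients are affected. This is possible, but nothing shows it. One slip in the article fits uniform delivery equally well.
- That no result could be tied to a known exposure. This would need the delivered duration to be both variable and unrecorded. Neither is shown, and the case report form is not at hand.

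The reply does not remove the core. Restoring a lost unit leaves the conflict with one hour. The reference to earlier work concerns the delivery method, is not at hand, and cannot make the two sections agree. An analysis plan could supply adherence rules, but it would not remove the contradiction from the protocol text. The point is two incompatible statements, not an omitted detail.

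**Conclusion.** The point holds as an internal inconsistency. The article states the duration of the experimental exposure in two incompatible ways, and no other section resolves it. The difference is fourfold if the unit in the Interventions section is minutes; under any ordinary unit the two disagree. From this document a reader cannot tell which exposure the result will concern, or whether a xenon patient treated for one of the two durations counts as adherent in the per-protocol analysis.

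The effect is limited. The randomised comparison in the full analysis set keeps its membership, and the sample size does not depend on duration. Confidence is high for the textual conflict. Any effect on patients already treated is conditional on what was actually delivered. The inconsistency should still be corrected, because a figure that the trial relies on is at issue and correction costs very little.

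**What to change.** 1. Reconcile the Interventions section and the Discussion with the ethics-approved protocol. State the duration once, with its unit and its start and stop points. This review does not say which value is right; the documents do not show it.
2. Before the unblinded interim analysis, define duration-based adherence for the per-protocol set against the reconciled figure.
3. Also before that analysis, check the recorded exposure of the xenon patients among those already enrolled.
4. If exposures turn out to have differed, keep every patient in the full analysis set as randomised and report the exposure delivered.

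The cost is a text correction, one added sentence in the definition of the per-protocol set, and a check of existing records. Sample size, randomisation and the primary test stay as they are.
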